## Methods

### Design and setting

The clinical trial was designed as a pragmatic, randomized, parallel two-arm, single blind trial to compare the individualized adjustment of acenocoumarol dosage using a pharmacogenetic algorithm versus the standard adjustment, in patients initiating oral anticoagulation for the treatment of venous thromboembolism. The follow-up period will be three months (Figure
1). The study will be performed in five separate hospital centers in the Community of Madrid (Spain). The recruitment period started in March 2011 and is scheduled to end in the fourth quarter of 2012.

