Inclusion phase (days −3 or −2): After recording in the case report file (CRF) that the patient meets the selection criteria, the patient's clinical situation will be reviewed and the following information about the medical history will be recorded in the CRF: personal history and anamnesis, including concomitant medication with current dosage and regimen, and complete physical examination which will include height and weight. The patient will also be provided with a card listing basic information about the trial, what to do in the event of severe adverse events and the research team's telephone numbers. The start of the treatment with acenocoumarol will occur on day −3 or −2, according to standard clinical practice. The following dosages will be provided to the researcher as a guideline for the local recommendations: 2 mg a day for patients below 65 years of age and 1 mg a day for older patients or those with risk factors.

Pharmacogenetic specimen collection: During recruitment, a blood sample will be taken from the patient (two tubes of 5 mL EDTA K3) and will be sent by messenger to the laboratory where the patient's genotype will be determined.

The samples do not require special conservation or transportation conditions. In the event that the messenger collects the sample the day after extraction, it is recommended that the blood sample be stored in a refrigerator.

The results will be sent by email within 48 hours. The medical monitor will ensure compliance with these deadlines and will solve any logistical problems that may arise.

Individualization phase:

Day 0:

– Control group: The INR will be determined in a capillary blood sample by means of a CoaguCheck® portable coagulometer (Roche FarmaSA, Madrid, SPAIN), and the acenocoumarol dosage will be determined according to standard clinical practice.

– Intervention group: At this time, the results of the genotyping will have returned and the acenocoumarol dose will be calculated according to the developed algorithm.

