### Randomization

The randomization was performed using a masked randomization scheme, in a 1:1 ratio, in blocks of four patients and stratified by center. Based on this scheme, randomization envelopes were created for each center. The patient's code was written on the outside of these envelopes (center and patient codes) and inside the opaque sealed envelope was a card indicating the study group to which the patient was assigned. The envelopes and card were stored in the investigator file.

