### Genotyping

In the recruitment visit, two 3 ml tubes of blood will be collected from all participants for genotyping of *CYP2C9*2* (rs1799853), *CYP2C9*3* (rs1057910), *VKORC1* (*−*1639 G *→* A = rs9923231), *CYP4F2* (rs2108622), and *APOE* (8016 C *→* T = rs7412), using a previously developed multiplex technique
[28]. Measurements will be performed in a centralized manner at the Laboratory of Population Genetics of the Department of Forensics at the Universidad Complutense de Madrid.

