### Statistical analysis

All recruited patients will be included in the main analysis, following an ‘intention to treat’ (ITT) strategy. For the ITT analysis, patients lost to follow up will be classified in the following way: 1) patients lost before the seventh day will be considered to be outside the therapeutic range; 2) patients lost before the last visit and that have not reached the stable INR will be considered not to be in stable dosing; 3) all lost visits, the INR will be accounted as being out of the therapeutic range. In addition, we will perform a per protocol analysis on all patients who can be monitored for the three month period planned for the study and who have not missed more than one intermediate follow-up visit.

To compare the analysis variables between both groups, a contrast test of the hypothesis will be appropriate based on the normality of the sample (Kolmogorov-Smirnov test), with a Cox regression for dichotomous variables or Kaplan-Meier curves for representing results whenever possible. A regression model (linear or logistic, as appropriate) will be performed when necessary to correct for possible confounding factors. To determine the difference between the two groups in the proportion of time within the therapeutic range, we will use the linear interpolation method proposed by Rosendaal *et al*.
[27]. Finally, we will perform a regression model stratified by center. The value *P* <0.05 will be established as statistically significant, adjusting for multiple comparisons whenever necessary.

The cost-effectiveness analysis will be performed according to a parallel and independent protocol, with special consideration of the direct costs associated with the health care of these patients.

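### Randomisation is stratified by centre, but the described group comparison leaves centre out, covariates enter only if the data seem to call for them, and no analysis is named as the main one

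*Protocol article*

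**What the plan says.** The Randomization section of the protocol article allocates patients "in a 1:1 ratio, in blocks of four patients and stratified by center". Design and setting gives five hospitals in the Madrid region.

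The Statistical analysis section then lists three kinds of analysis:

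1. A two-group test, not named, chosen after a Kolmogorov-Smirnov check. Centre is not mentioned.
2. A linear or logistic regression that "will be performed when necessary to correct for possible confounding factors". The factors are not listed.
3. "Finally, we will perform a regression model stratified by center". The outcome it applies to, and whether it is primary or supportive, are not given.

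No sentence ranks the three. Baseline information is collected in both arms. Study procedures records history, medication, height and weight, and its start-up guidance distinguishes "2 mg a day for patients below 65 years of age and 1 mg a day for older patients or those with risk factors". In the Genotyping section, "two 3 ml tubes of blood will be collected from all participants for genotyping".

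**The concern.** Stratifying the randomisation by centre balances the arms within each centre. If in-range rates differ between centres, the estimated difference then varies less than a pooled formula assumes. The analysis recovers that precision only if it takes centre into account, and here centre appears only in a last model of undefined status.

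The covariate rule is a separate weakness. In a randomised trial any baseline imbalance is due to chance, so adjustment serves precision and belongs in the plan beforehand. A rule that adjusts when it seems necessary makes the model depend on the data, and with no covariate list it leaves several candidate results for one endpoint.

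At stake are some avoidable loss of power in one direction and a loosely held 5% error rate in the other.

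**Working it through.** **Inputs from the article (Sample size calculation, Randomization, Design and setting).** 40% versus 60% in range on day 7; alpha 0.05; beta 0.2; 97 completers and 120 recruited per group; five centres; blocks of four.

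**Assumptions.** The article gives neither the spread of in-range rates between centres nor the strength of any covariate. Centre spread is taken as a logit-scale SD of 0 to 0.8, with five equal centres of 24 per arm. At SD 0.8 the control rates by centre are 16, 28, 39, 50 and 67%.

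**Step 1: the plan's own figures.** Two-sided, pooled variance, no continuity correction:

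n = [1.960·√(2·0.5·0.5) + 0.842·√(0.4·0.6 + 0.6·0.4)]² / 0.20² = (1.386 + 0.583)² / 0.04 = 96.9, so 97. This matches.

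Time to stable INR: n = 2·(1.960 + 0.842)²·21² / 10² = 69.2, so 70. This matches.

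The first formula contains no centre term, so the sample size does not rely on stratification.

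**Step 2: why ignoring centre inflates the standard error.** With the arms balanced within equal centres and in-range rates p_k, the pooled test uses the variance p̄(1−p̄). The true variance uses p̄(1−p̄) − Var(p_k). The standard error is therefore too large by the factor √{p̄(1−p̄) / [p̄(1−p̄) − Var(p_k)]}.

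At SD 0.8 with no treatment effect: p̄ = 0.40 and Var(p_k) = (0.0576 + 0.0144 + 0.0001 + 0.0100 + 0.0729)/5 = 0.031. The factor is √(0.24/0.209) = 1.07. The effective critical value becomes 1.96·1.07 = 2.10, which corresponds to a type I error of about 3.6%.

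**Step 3: simulation.** The pooled two-proportion test was compared with Cochran-Mantel-Haenszel by centre, 120 per arm, 40,000 runs per setting (Monte Carlo error about 0.1 point at 5%).

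| Centre SD (logit) | SE of difference, pooled / stratified | Excess | Power, pooled / stratified | Type I error, pooled test |
|---|---|---|---|---|
| 0 | 0.0630 / 0.0632 | 0% | 86.9% / 87.0% | 5.3% |
| 0.3 | 0.0630 / 0.0626 | 1% | 87.3% / 88.3% | 4.8% |
| 0.5 | 0.0630 / 0.0614 | 3% | 87.6% / 89.7% | 4.7% |
| 0.8 | 0.0630 / 0.0590 | 7% | 88.3% / 91.5% | 3.7% |

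An extreme SD of 1.2 (control rates 9 to 77%) gives 14% excess, power of 89.9% against 94.8%, and type I error of 2.6%. With 95 per arm, close to the 97 completers, power at SD 0.8 is 81.1% against 84.6%.

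**Step 4: the effect of choosing among analyses.** With no treatment effect:

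- Rejecting if either the pooled or the centre-stratified test rejects gives a type I error of 4.8 to 5.4% over all these settings. That is essentially no inflation.
- Taking the best of three analyses (unadjusted, centre-stratified, full covariate model) gives about 6% (2,500 runs, Monte Carlo error about 0.5 point).
- Taking the best of six (unadjusted, centre only, one, two or three assumed covariates, and centre plus all three) gives 6.6 to 7.9% (6,000 runs per setting).

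The inflation therefore comes from the open covariate choice, and its size depends on how strong the covariates are assumed to be.

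**The case against.** The strongest case against the point runs as follows.

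- **The text does not call any test unstratified.** It commits to a centre-stratified regression, and the word introducing that sentence may mark its order and not its rank. This stands: that the main comparison ignores centre is an inference. What remains is that the described group comparison omits centre and the centre model has no stated role.
- **Too-wide intervals are not established.** A reader might infer that the trial's confidence intervals will be too wide. That requires real differences between centres, which the article does not report. Five hospitals in one region, referred to one local guideline, may differ little. This stands too, and the loss may be close to nil.
- **Omitted covariates do not make the test conservative.** Only ignoring the stratification factor does. Leaving out a covariate not used in the randomisation keeps the error rate nominal and costs precision. This is correct, so larger power gains obtained by also assuming strong predictors should not be credited to centre.
- **A condensed article may leave covariates and model labels to the full protocol or analysis plan.** This is true of omissions. It does not cover a rule that the article states, and states in data-dependent form.
- **Adjusting for start-up dose or predicted dose has its own problems.** The envelope is opened at inclusion, physicians are not masked, and Definition of the intervention says that the algorithm regimen also uses INR. The dose actually given, or an INR-updated prediction, could therefore reflect events after randomisation. The variance explained that the Background reports concerns stable dose, not day-7 status. This stands: such covariates are optional and must be defined from baseline values.

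**Conclusion.** The point holds as a modest, inexpensive improvement. The stated analysis does not carry the randomisation factor into an identified main comparison, and its covariate rule is triggered by the data.

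The two effects pull in opposite directions, and both are small. The cost of ignoring centre is nil if centres do not differ and reaches the upper end of the range only if control rates run from about 16 to 67% across centres, an assumed spread for which the article gives no evidence. The excess error from choosing among covariate models is one to three percentage points, and arises only if the most favourable result is reported.

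Two stronger conclusions are not supported. The sample size is not undermined: it reproduces without using centre, and the error from ignoring centre is on the safe side. Nor does having both an unstratified and a centre-stratified test available threaten the 5% level by itself.

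**What to change.** - Name one main analysis of day-7 in-range status that is stratified by or adjusted for centre, for example a Mantel-Haenszel risk difference, or a logistic regression with centre reported as a marginal risk difference, with a 95% confidence interval.
- Stratify the analysis of time to stable INR by centre.
- Delete the conditional wording on confounders. If covariates are wanted, list them in advance and use only values fixed before randomisation, such as age or the age/risk-factor category, and genotype. Do not use the dose actually given or a predicted dose updated with INR.
- Report the unadjusted comparison, and any other model, as supportive.

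The cost is a change of wording and slightly more analysis work. The data are already collected in all participants. The Trial status section reports 85 patients included and recruitment continuing, so the change could be made before the final data are seen.

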**Methods and design:**

This is a multicenter, single blind, randomized controlled clinical trial. The protocol has been approved by La Paz University Hospital Research Ethics Committee and by the Spanish Drug Agency. Two hundred and forty patients with VTE in which oral anticoagulant therapy is indicated will be included. Randomization (case/control 1:1) will be stratified by center. Acenocoumarol dose in the control group will be scheduled and adjusted following common clinical practice; in the experimental arm dosing will be following an individualized algorithm developed and validated by our group. Patients will be followed for three months. The main endpoints are: 1) Percentage of patients with INR within the therapeutic range on day seven after initiation of oral anticoagulant therapy; 2) Time from the start of oral anticoagulant treatment to achievement of a stable INR within the therapeutic range; 3) Number of INR determinations within the therapeutic range in the first six weeks of treatment.

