### Assessment variables

#### Effectiveness variables

##### Primary

• Percentage of patients with an INR within the therapeutic range (INR between 2 and 3) on day seven after the initiation of treatment with acenocoumarol.

• Time from the start of the oral anticoagulant therapy to get a stable INR within the therapeutic range (INR within the therapeutic range for three consecutive measurements for at least two weeks, with a maximum difference between the daily average doses of 10%).

• Number of INRs within the range in the first six weeks of treatment.

• Number of INRs within the range during the three months of the study.

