### Sample size calculation

We need 97 subjects per group to complete the study in order to detect an absolute difference of 20% in the number of patients who are within the therapeutic range on the seventh day after starting the treatment. For this calculation, we have set an alpha error of 0.05 and a beta error of 0.2, and we assume that 40% of the patients will be within the desired INR, and expect this to increase to 60% in the experimental group. Given the risk of drop-out, the number of patients per group will increase by 20%, placing the recruitment objective at 120 patients per group.

According to Caraco *et al*.
[31], pharmacodynamic stabilization with warfarin in the standard control group was achieved in 40.2 ± 21 days. For a reduction in ten days in the experimental group and alpha and beta errors of 0.05 and 0.2 respectively, the required number of patients per group will be 70.

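### Four unranked primary variables (three in the abstract) have no success rule, and the sample size uses the full 0.05 for two of them, so the error rate and the 80% power are not jointly secured

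*Protocol article*

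**What the plan says.** The protocol article bears on this in four places.

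- **Effectiveness variables, Primary.** Four variables are listed without rank: the percentage of patients in range on day 7, the time to a stable INR, the count of in-range INRs to six weeks, and a fourth, "Number of INRs within the range during the three months of the study".
- **Abstract, Methods and design.** The main endpoints stop at the third: "3) Number of INR determinations within the therapeutic range in the first six weeks of treatment". The three-month count is absent.
- **Sample size calculation.** For day 7, "we have set an alpha error of 0.05 and a beta error of 0.2". The in-range rates behind it are 40% for controls and 60% under the algorithm. This leads to "We need 97 subjects per group to complete the study". A second calculation, for time to stability, uses the same alpha and beta and gives 70 per group. Neither INR count has a calculation.
- **Statistical analysis.** The threshold is P <0.05, "established as statistically significant, adjusting for multiple comparisons whenever necessary". No method, order of testing or lead variable is given.

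The Objectives section has one primary objective, effectiveness of the algorithm. It does not say which variables, or how many, must be positive to meet it.

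**The concern.** A reader of the final report needs to know what result would have made the trial positive. Here that cannot be determined, because the article disagrees with itself on the number of primary variables and has no rule joining them.

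The sample size and the multiplicity sentence also do not fit together. The calculation leaves no alpha for any other primary variable, while the analysis section allows for an adjustment that the calculation did not budget for. If no adjustment is made and any one success counts, the false-positive risk exceeds 5%. If alpha is split, day 7, which sets the recruitment target, loses power. The Masking section concedes that physicians are not blinded, which is a further reason to settle the rule before results are seen.

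**Working it through.** **Inputs from the article.** Day-7 rates 40% and 60%; alpha 0.05; beta 0.2; 97 per group completing and 120 recruited; 1:1 allocation. For time to stability: SD 21 days ("pharmacodynamic stabilization with warfarin in the standard control group was achieved in 40.2 ± 21 days"), a reduction of 10 days, and the same alpha and beta. The article does not state sidedness; two-sided reproduces both sample sizes.

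**1. The article's own figures.**

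Day 7, pooled variance, no continuity correction:

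n = [z₀.₉₇₅·√(2·0.5·0.5) + z₀.₈₀·√(0.4·0.6 + 0.6·0.4)]² / 0.2²
= [1.960·0.7071 + 0.8416·0.6928]² / 0.04 = 96.9, so **97**. It matches, with power 80.0%.

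Time to stability: n = 2·21²·(1.960 + 0.8416)² / 10² = 69.2, so **70**. It matches.

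Each figure is therefore right if its own variable carries the whole 0.05.

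**2. No adjustment, and any one success counts.**

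Independent tests: 1 − 0.95⁴ = **18.5%** for four; 1 − 0.95³ = **14.3%** for three.

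The article gives no correlations. With equal correlations assumed between normal test statistics (1,000,000 simulated draws):

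| Assumed correlation | Four tests | Three tests |
|---|---|---|
| 0.3 | 17.4% | 13.5% |
| 0.5 | 15.6% | 12.5% |
| 0.7 | 13.0% | 10.9% |
| 0.9 | 9.4% | 8.4% |

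**3. Equal split of alpha (Bonferroni, an assumption).**

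Day-7 power = Φ{[0.2·√n − z·0.7071] / 0.6928}. For four variables alpha is 0.0125 and z = 2.498:

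- n = 97: Φ[(1.970 − 1.766)/0.6928] = Φ(0.294) = **61.6%**
- n = 120, all evaluable: Φ[(2.191 − 1.766)/0.6928] = Φ(0.613) = **73.0%**
- n for 80%: (1.766 + 0.583)²/0.04 = 138 per group

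For three variables alpha is 0.0167: 65.5% at 97, 76.4% at 120, and 130 per group needed for 80%.

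Time to stability at alpha 0.0125 and 97 per group: Φ[10/(21·√(2/97)) − 2.498] = Φ(0.819) = **79.3%**. The loss therefore falls mainly on day 7.

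**The case against.** **The article does foresee adjustment.** This stands in part. The clause sits in the same prospective sentence as the 0.05 threshold. A reader might infer that all four variables are to be tested unadjusted, or that the decision is to be made after seeing the data; the text says neither. It also does not say when adjustment is needed or how it would be done.

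**The method may be in the full protocol or analysis plan.** This is fair for the choice of correction. It does not cover the mismatch between four and three primary variables, or the full alpha being used for two of them, because both are in the text shown.

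**No stated figure is wrong.** This stands. A reader might infer that either the 5% or the 80% must be false. That does not follow: with day 7 as single lead variable, or first in a fixed order, both hold at the planned size. Requiring all four to succeed would also control the error rate, although 80% power for the whole set would not have been shown.

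**18.5% is too high for these variables.** As an estimate, yes; it is an upper figure. Five of the seven scheduled INRs (days 0, 3, 7, 15, 30) enter both counts, and day 7 is one of them. If visit results are taken as independent with equal variance, the two counts correlate at √(5/7) = 0.85, and day 7 correlates at √(1/5) = 0.45 and √(1/7) = 0.38 with the six-week and three-month counts. With time to stability correlated 0 to 0.7 with all three (assumed), simulation gives 15.9% down to 13.4%. That is lower than 18.5% but still far above 5%.

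**62% is a harsh figure.** It depends on Bonferroni, which the article does not name, and on 97 analysed. The intention-to-treat analysis keeps all recruited patients and counts losses before day 7 as out of range. With 120 per group and an assumed 2% to 5% lost by then, both rates shrink by that fraction and power at 0.0125 is about 71% to 68%. It remains below 80%.

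**Conclusion.** The point holds as a missing success rule combined with an inconsistent primary set. It is not an arithmetic error: 97 and 70 both reproduce.

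- If one unadjusted success out of four is enough, the family-wise error lies between about 9% and 18.5%, depending on correlation. About 13% to 16% is plausible given the overlap of the variables. All correlations are assumptions.
- If alpha is split equally over four, day-7 power is about 62% at 97 completers and 73% with all 120 per group evaluable, against the stated 80%. Time to stability keeps about 79%.

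Nothing in the article says which of these situations applies, or that day 7 leads. The matter should be settled before analysis, because it decides what counts as a positive trial.

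**What to change.** 1. Name the day-7 in-range percentage, on which recruitment is sized, as the single primary variable at two-sided 0.05.
2. Test the other three in a prespecified order, each at 0.05 and only if the one before it is significant. One possible order is time to stable INR, then the six-week count, then the three-month count. The order is for the sponsor to choose.
3. Make the abstract and the Primary list agree, and replace the open-ended adjustment clause in the Statistical analysis section with this rule.
4. Issue this as an amendment documented as made without sight of comparative results. The Trial status section reports 85 patients already included and recruitment continuing, and physicians know the allocation.

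**Cost.** No extra patients: 97 completing and 120 recruited per group stay as planned, with 5% and 80% both kept for day 7. An equal split over four would instead need 138 completing per group, or 173 recruited with 20% loss (138/0.8 = 172.5). The price of the fixed order is that no lower-ranked variable can be claimed as confirmatory if day 7 fails, and that the primary set changes during recruitment.
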